##### Positive Affect and Negative Affect-Extended

The Positive Affect and Negative Affect-Extended (PANAS-X) instrument consists of 30 items and captures the valence (positive and negative) and the arousal (activated or deactivated) of the mood descriptors. As a result, PANAS-X30 makes it possible to measure positive (pleasant) and negative (unpleasant) and within both activated and deactivated affect states. This distinction is relevant in yoga studies, where effects are likely to be found in pleasant, deactivated emotions such as feeling calm, content, and relaxed. The following are examples for all four categories. Positive activated: *active, enthusiastic, excited, inspired* and, *proud*; Positive deactivated: *at ease, serene, calm, relaxed*, and *content*; Negative activated: *afraid, scared, hostile, guilty*, and *ashamed*; Negative deactivated: *tired, sluggish, drowsy, dull*, and *bored* (38).

The four scales' internal consistency is acceptable, with Cronbach's alphas ranging from 0.77 to 0.88 (25).

##### Brief Symptom Inventory

The Brief Symptom Inventory (BSI) is a self-rated measure of general psychopathology and psychological distress (39). The BSI contains 53 items reflecting psychological symptom patterns of psychiatric patients and non-patients. It comprises nine primary symptoms' scales and the global severity index (GSI). The primary symptom scales are: Anxiety, Depression, Interpersonal Sensitivity, Hostility, Obsessive Compulsiveness, Psychoticism, Paranoid Ideations, Phobic Anxiety, and Somatization. The answers are given on a five-point scale, from 0 = “not at all” to 4 = “extremely.” The BSI subscales and its GSI have high internal reliability (0.71–0.85) (9, 40, 41) and test-retest reliability, as well as high convergent, discriminant, and construct validity (42).

##### Pain

The Pain assessment instrument uses verbal and numerical assessment scales, where the participant describes their pain during the last two weeks using words (*no pain*; *mild pain*; *moderate pain*; *severe pain*; *very severe pain*; *unbearable pain*) and using numbers between 0 and 10, where 0 (zero) represents no pain, and 10 represents the worst possible pain. The type of pain and its location is marked by the participants on a standard image of a man or a woman (43).

##### Brief Substance Craving Scale

There have been multiple recommendations that craving should be included as a standardized outcome in treatment studies (44). The Brief Substance Craving Scale (BSCS), designed by Somoza et al. (45), will be used in the present study to measure the intensity, frequency, and lengths of cravings in the participants. BSCS measures craving for the primary substance, including alcohol and drugs. This short, self-report measure has previously been used and tested for psychometric properties (46, 47).

##### Self-Directedness

Self-directedness (SD) is a personality trait of self-determination. It captures the participant's ability to regulate, control, and adapt his/her behavior to situational requirements with the aim to achieve personally chosen goals. It is one dimension in Cloninger's Temperament and Character Inventory (TCI) (48). Cloninger has described SD as “willpower.” It captures to what extent a person identifies themself as an integrated, purposeful, self-sufficient, self-acceptant, responsible, reliable, and effective individual. SD contains 20 questions of the TCI-R140 scale.

##### Interviews

After the intervention (six weeks of yoga) qualitative information will be gathered about the participants' experience of yoga and possible health effects (please see the Supplementary Material for the semi-structured interview guide).

#### B. Heart Rate Variability

Heart rate variability (HRV), or the beat-to-beat alteration in heart rate, offers a noninvasive indicator of the autonomic nervous system's activity (49). HRV has been used as a proxy for health and fitness and as an indicator of autonomic regulation. Low HRV—indicating reduced parasympathetic cardiac control—was associated with sleep problems and difficulty regulating emotions (50), while yoga practice was associated with increased HRV (51).

HRV can be measured with a good quality activity bracelet and an App belonging to that, recording an electrocardiogram. At the moment we do not know which algorithmic approach for operationalizing HRV will be used. Data will be recorded during the first and last occasions of the intervention (yoga class). HRV data for the comparison group will be recorded with an identical time interval, during leisure time physical activity.

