### Procedure

Upon placement to the juvenile institution, the young people will be offered to participate in the study. Participation is voluntary, and SiS clients are ensured that participation in yoga or in a comparison group or non-participation should not affect the care they receive at SiS. All data is coded (pseudo-anonymized) and the code keys will be kept securely at each juvenile institution under the institution directors' responsibility, following SiS regulations. Upon completion of data assessment code keys will be destroyed. Only anonym data will be handled outside each SiS facility. With this procedure we assure that there is no possibility of identifying the individual from the collected information.

The study has a *quasi-experimental* design. Participants will receive a numeric code and will participate in the pre-intervention assessment, after which they will chose to participate in yoga classes (belonging to the “yoga group”) or not to participate in yoga classes (belonging to the “comparison group”) (Figure 2). The yoga group will participate in a 75 min yoga session, twice a week, for six weeks—as their leisure-time physical activity. During the same six-week period, the comparison group will participate twice a week (~1 h) in any, at the institution offered leisure-time physical activity (e.g., walking, gym training, and physical education class). Participants of the comparison group are asked to include ~10–15 min of relaxation at the end of their leisure-time physical activity.

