### Yoga Classes

The yoga classes held twice a week consist of trauma-informed yoga methods including inviting language, freedom of choice by offering options, a set routine for predictability and recognition, counting down in challenging poses for a sense of control and guidance toward practical interoceptive awareness. The relaxation offered is a progressive muscle relaxation adapted for ADHD and high anxiety levels. The aim is to increase resilience, promote relaxation and to provide self-regulation skills for stress and overwhelming emotions and reactions promoting self-empowerment and impulse control. The class will be set up in a circle to provide a sense of safety with no outer disturbances for triggering responses and will always be offered on a voluntary basis for the participants.

A yoga class is 75 min long and consists of yoga methods such as physical movement, static yoga postures, balance exercises, and breathing practices. The instruction intends to increase the interoceptive awareness with practically adapted mindfulness and guided trauma-informed progressive relaxation. The class includes intervals of raising and lowering heart rate and breathing to provide self-regulating skills. The classes do not consist of potential triggering poses, no physical adjustments or practices that can bear a resemblance to sexual abuse or practices that can over-activate the sympathetic nervous system.

Each class is built up as follows:

Warm-up 15 min: At least 10 min of warm-up exercises to release muscular tension, discharge high-stress levels, restlessness, and anxiety, increase blood circulation, and increase proprioceptive awareness.Opening sequence 15 min: large energizing dynamic movements.Balancing poses 10 min.Dynamic Sequence 15 min: a combination between dynamic energizing movements and powerful postures where the participants hold the pose for at least two min (impulse-control). The importance of synchronized breathing and movements.Closing 20 min: including the last 10 min with guided mindfulness-based relaxation.

The instructors have completed a special training program in trauma-informed yoga and yoga for mental health, and they are trained in how to manage overwhelming emotions in a class. The classes are adapted to the most common mental health issues presented within the juvenile institutional system, such as PTSD, anxiety disorders, depression, ADHD, and autism.

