### Measures

Three different origins of data are included as measurements: (A) self-reported measures in the form of a survey, (B) heart rate measure, and (C) register data. A and B applied both at pre-intervention (Test 1) and post-intervention (Test 2), while the data from SiS's register will be combined with data only for those participants who complete all parts of the study.

The pre-intervention survey includes a question on yoga expectations, and the post-intervention assessment includes a question on time spent on yoga and the experience of yoga.

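### HRV is recorded during different activities in the two groups, and first inside session one, so a group difference in level cannot be separated from the activity and there is no pre-intervention baseline.

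*Protocol article*

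**What the plan says.** All references are to the Protocol article.

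- **Purpose.** Section B, Heart Rate Variability, states: "HRV has been used as a proxy for health and fitness and as an indicator of autonomic regulation".
- **Recording, yoga group.** The same section: "Data will be recorded during the first and last occasions of the intervention (yoga class").
- **Recording, comparison group.** "HRV data for the comparison group will be recorded with an identical time interval, during leisure time physical activity". Procedure allows any activity on offer at the institution, described as "leisure-time physical activity (e.g., walking, gym training, and physical education class").
- **Content of the yoga class.** Yoga Classes: "The class includes intervals of raising and lowering heart rate and breathing to provide self-regulating skills".
- **Timing.** Measures lists the survey as A and heart rate as B, and says "A and B applied both at pre-intervention (Test 1) and post-intervention (Test 2"). Assessment places Test 1 before the intervention and Test 2 after six weeks of it, with every measure included in both. Procedure has participants choose their group only after the pre-intervention assessment.
- **Metric.** "At the moment we do not know which algorithmic approach for operationalizing HRV will be used".
- **Analysis.** Data Analysis compares Test 1 with Test 2 within groups by Wilcoxon signed-rank test, calculates mean changes, and compares groups by Mann–Whitney test without saying whether on levels or on changes. BSI is primary. The secondary outcomes named are craving, pain, affect and aggressive antisocial behaviour.

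**The concern.** HRV is meant to say something about autonomic regulation, yet the recording condition is tied to group membership. One group is measured while a class deliberately moves heart rate and breathing up and down. The other is measured during whatever activity each participant has taken up. The identical time interval equalises timing. It does not equalise exertion, posture or breathing.

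The timing raises a separate problem. A recording made inside the first class comes after the group choice and during exposure, so it cannot also be the Test 1 measurement taken before the intervention.

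At stake is the trial's only physiological measure, beside self-report and register data. If data are collected as section B describes, no later analysis can recover the missing pre-intervention values.

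**Working it through.** **1. The plan's own figure.** The only calculation in the document is the sample size of 34 per sex. For the within-between interaction, λ = f²·N·m/(1−ρ). With f = 0.25, m = 2, N = 34 and an assumed ρ = 0.5, λ = 0.0625 × 34 × 2 / 0.5 = 8.5 on 1 and 32 degrees of freedom. Power is 0.807, and N = 32 gives 0.781, so 34 reproduces. It has no bearing on HRV, for which the document gives no figures.

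**2. The timing, side by side.** Procedure gives the order: pre-intervention assessment, group choice, then sessions. Assessment and Measures put heart rate in the pre-intervention assessment. Section B puts the first recording in the first session, which can only follow the choice. Both cannot hold. This needs no arithmetic.

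**3. Effect of the activity on the contrast.** Suppose yoga has no effect on HRV and the more vigorous comparison activity shifts HRV by s standard deviations relative to the class. Let p₁ and p₂ be the shares of comparison participants in that activity at the first and last recording. Then:

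- spurious difference in last-occasion level = s·p₂
- spurious difference in change = s·(p₂ − p₁)

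The level difference is zero only if nobody carries a shift. The change difference is zero whenever p₁ = p₂.

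**4. Simulated false rejection.** Inputs from the document: 120 participants and up to 50% attrition (Participants), so 120 × 0.5 = 60 completers. Assumed: an equal split (30 per group), normal values, first-last correlation 0.5, s = 0.5, 1 or 2, and the shares below. Mann–Whitney test at 5%, 1,500 runs per row.

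| Comparison activity | s (SD) | Level difference, s·p₂ | Level test rejects | Change difference, s·(p₂−p₁) | Change test rejects |
|---|---|---|---|---|---|
| All shifted both times (p₁ = p₂ = 1) | 0.5 | 0.50 | 44.5% | 0 | 5.7% |
| | 1 | 1.00 | 96.0% | 0 | 4.3% |
| | 2 | 2.00 | 100% | 0 | 5.1% |
| Mixed, stable share (p₁ = p₂ = 0.5) | 0.5 | 0.25 | 15.5% | 0 | 5.5% |
| | 1 | 0.50 | 40.3% | 0 | 5.2% |
| | 2 | 1.00 | 82.9% | 0 | 5.8% |
| Share drifts (p₁ = 0.4, p₂ = 0.7) | 0.5 | 0.35 | 24.0% | 0.15 | 9.1% |
| | 1 | 0.70 | 68.5% | 0.30 | 18.1% |
| | 2 | 1.40 | 98.7% | 0.60 | 39.8% |

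With s = 0, both tests stay at 3.5–5.7%, as they should. The simulated mean differences agree with the formulas to within 0.01 SD.

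**The case against.** The strongest reply is that the trial looks at change. Data Analysis compares Test 1 with Test 2 and calculates mean changes, and a first-to-last contrast cancels a constant activity effect. This stands: the change test holds its level in every stable-mix row above. It does not settle the matter, because the comparison activity is open to choice on each occasion and Data Analysis does not confine the between-group test to change. A comparison of levels is neither confirmed nor excluded.

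Second, both groups end with a calm phase: "Participants of the comparison group are asked to include ~10–15 min of relaxation at the end of their leisure-time physical activity", and the yoga class closes with 10 minutes of guided relaxation. An article may leave the exact recording window to the full protocol. That is fair, but section B names the class and the activity as the recording setting, and a window at the end of a session would still not be a measurement before the intervention.

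Third, HRV is peripheral. It is absent from the hypotheses in the Abstract and from the outcomes named in Data Analysis. This stands and limits the importance of the point.

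A reader might infer that the measure captures only the activity, or that it can support no conclusion at all. The documents do not bear that out. The yoga manual is standardised and the class follows a fixed timed sequence, so the yoga group's own first-to-last change is taken under similar conditions and can be read descriptively, though without a control. Nor do the documents show which group exerts itself more: the class has energetic sequences, and the comparison activities include walking. The direction of any bias is therefore unknown.

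**Conclusion.** The point holds in three parts.

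- A between-group difference in HRV level cannot be separated from the activity under way.
- A difference in change is protected only if the comparison group's activities are alike at both recordings, which nothing in the document secures.
- Section B contradicts Assessment, Measures and Procedure on when the first recording is made. Following section B leaves no pre-intervention HRV baseline.

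The first and third parts rest on the text alone. The size rests on assumed shifts and an assumed drift: false rejection of 45% to 100% for levels when all comparison participants carry the shift, nominal for change with a stable mix, and 9% to 40% for change under drift from 40% to 70%. Smaller shifts or less drift would give less.

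HRV is neither the primary outcome nor one of the listed secondary outcomes, and no sample size depends on it, so the trial's main conclusion is unaffected. The change is worth making because it is cheap and cannot be made after data collection.

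**What to change.** Reconcile Assessment, Measures and section B by recording HRV in both groups at Test 1 and Test 2 under one standardised resting condition: same device, posture and duration, before any activity. State that groups are compared on change from that baseline. Keep recordings made during sessions as description only.

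The cost is a few extra minutes and some scheduling of devices at two assessments already planned.

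If resting recordings are not feasible, prespecify a common window in the closing relaxation phase that both groups have. This would reduce the mismatch in recording conditions but would not restore a pre-intervention baseline, and the article should then say so and stop describing the first HRV recording as a Test 1 measure.

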#### C. Register Data

Register data concerning the participants' medications during the intervention, their school attendance and participation in physical activity classes during the study will be assessed based on registers kept by SiS.

### Data Analysis

If the required number of male and female participants (at least 34 of each gender) is reached, then we will analyze the data separately by gender. Otherwise, the data will be pooled, and no gender-specific results will be presented.

All statistical analyses will be conducted using a significance level of *p* <0.05. Only complete post-attrition data will be analyzed. The comparison of the attrition rates between the two groups (“yoga” group and “comparison” group) will be calculated using Fisher's exact test. The Test 1 and 2 scores within the groups will be compared using the Wilcoxon signed-rank test. Mean changes and standard deviations will be calculated to identify differences within the groups. Mann–Whitney *U-*tests will be used for the continuous variables and Fisher's exact test for the categorical variables to compare differences between them. The effect sizes (Cohen's *d*) will be calculated to identify differences between the groups; an effect size of 0.2 will be considered a small effect, 0.5 a medium effect, and 0.8 a large effect. As data will be collected from three institutions, generalized estimating equations (GEE), that adjusts standard regression estimators for clustering, will be applied. The primary outcome is the level of psychological distress (BSI). Secondary outcomes' (craving, pain, affect, and aggressive antisocial behaviors) mediating and moderating effect will be also explored by conditional process analyses. We plan to conduct a mid-point analysis (about nine months after that data collection has started) to allow for better modeling of change trajectories.

To describe the adolescents' experiences of participating in yoga practice, with the help of a semi-structured interview guide (Supplementary Material), individual interviews will be performed. The adolescents will be contacted within 2 weeks after completing the yoga intervention. Content analysis will be used as a method for analyzing the interviews (52). The qualitative content analysis is performed stepwise identifying meaning units, condensing the meaning units, labeling meaning units with codes and thereafter identifying subcategories, categories ant themes. Content analysis makes it possible to describe the adolescents' experiences on both manifest and latent levels.

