## Abstract

Recent studies have established yoga practice as a mainstream complementary clinical tool within correctional environments. It is shown that regular yoga practice is coupled with improved impulse control, sustained attention, attenuated antisocial and self-harm behaviors, reduced stress, and psychological distress. No academic research until now has provided evidence of mental health benefits of yoga for institutionalized young people. In Sweden, each year more than thousand adolescents receive compulsory care at juvenile institutions run by the Swedish National Board of Institutional Care. These young people are characterized by substance abuse, aggressive and antisocial behaviors, high frequency of self-harm, and the experience of abuse. Most of them manifest attention problems, depression, anxiety, and impulsivity. They have a dramatically increased risk for recidivistic criminal behavior, continuous medical, and social care and untimely death. The present study plan aims at evaluating, with previously validated psychological measures, in a quasi-experimental design, the effects of yoga practice for institutionalized adolescents. Adolescents' experiences of participating in yoga practice will also be assessed by semi-structured individual interviews. Ethical approval was given by the Swedish Ethical Review Authority. It is hypothesized that yoga practice (in combination with the standard treatment within institutional care) will reduce institutionalized adolescents' aggression, antisocial behavior, anxiety, depression, and negative affect, and increase their cognitive flexibility (in the form of increased impulse control).

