## Methods

### Participants

Computer required sample size analysis for repeated measures ANOVA within-between interaction, with an effect size of 0.25 [medium effect size; average from effect sizes in changes by yoga in previous studies (9, 25)], a power of 0.80, an alpha error probability at 5%, for two groups (yoga and comparison) and two measurements (pre-and post-intervention) suggested a sample size of 34 for each sex.

We aim to collect complete data from at least 34 participants of both sexes (34 male and 34 female clients) to perform gender-specific analyses. Gender analyses will only be performed, if this number of participants can be reached.

Based on previous experience working with participants within correctional settings, we know that the attrition rate can reach 50%; therefore, our aim is to include approximately 120 participants.

Three institutions at the South West in Sweden have at this stage declared interest in participating in the study. Data collection is planned to take place for one and a half years' time, based on an estimated three months per institute (Figure 1). This three months period includes spreading advertisements and information about the study, collecting informed consents, six weeks of intervention (including pre- and post-intervention tests), and time for qualitative interviews to assess individual experiences of yoga classes. As the average time spent within SiS is calculated to be eight months, we will be able to perform intervention and data collection in each participating institute twice, six months apart during the planned data collection period (one and a half years) (Figure 1).

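### If the gender targets are met, one hypothesis is tested twice at 5% each, and the plan does not say whether one significant gender confirms it

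*Protocol article*

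**What the plan says.** The Participants section sizes the study separately for each sex. It uses a repeated-measures ANOVA within-between interaction, "with an effect size of 0.25" and "a power of 0.80", and continues: "an alpha error probability at 5%, for two groups (yoga and comparison) and two measurements (pre-and post-intervention) suggested a sample size of 34 for each" of the two sexes. The aim is complete data on 34 males and 34 females, from about 120 recruits, with attrition that may be as high as 50%.

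The Data Analysis section then gives the rule: "If the required number of male and female participants (at least 34 of each gender) is reached, then we will analyze the data separately by" (that is, gender). If the numbers fall short, the data are pooled and gender-specific results are not reported. The same section says: "All statistical analyses will be conducted using a significance level of *p* <0.05". It names psychological distress on the BSI as the primary outcome.

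The hypothesis in the Abstract is not split by gender. It says that yoga, added to standard care, "will reduce institutionalized adolescents' aggression, antisocial behavior, anxiety, depression, and negative affect", among other effects.

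**The concern.** The pooled test, which matches the single hypothesis, is kept only for the case where recruitment falls short. When recruitment succeeds, it gives way to a male test and a female test of the same primary outcome, each at the full 5%. The article gives no split of alpha, no order between the genders and no rule for a result that is significant in one gender only.

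This affects what the trial can conclude. The Discussion links confirmation of the hypothesis to the value of yoga within juvenile institutional care nationally. If one significant gender out of two may be reported as confirmation, the error rate of that claim is higher than for a single test at 5%. A split result would also be easy to read as a gender-specific effect, which two separate p-values cannot show.

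**Working it through.** **Inputs.** From Participants: alpha 0.05 per sex, power 0.80, f = 0.25, two groups, two measurements, 34 per sex, about 120 recruits, attrition up to 50%. From Data Analysis: p < 0.05 for all analyses, and separate analyses once each gender reaches 34. The pre-post correlation ρ is not given. I assume 0.5 and show 0.3 to 0.7.

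**1. The plan's own figure.** For the within-between interaction, λ = f² × N × m / (1 - ρ), with df1 = 1 and df2 = N - 2. With N = 34, m = 2 and ρ = 0.5, λ = 0.0625 × 34 × 2 / 0.5 = 8.5 on 1 and 32 df. Power at alpha 0.05 is 0.807, and 34 is the smallest even N that reaches 0.80. The stated 34 per sex reproduces, with 5% spent in each sex.

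**2. When the branch applies.** Separate analysis needs at least 34 + 34 = 68 completers. From 120 recruits, attrition may be at most 1 - 68/120 = 43.3%, and then only with an even gender split. At 50% attrition 60 complete, and the data are pooled.

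**3. False-positive rate if there is no effect in either gender.** No participant is in both samples, so the tests are treated as independent. One primary test per gender is assumed.

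| Rule for confirming the hypothesis | Calculation | Chance |
|---|---|---|
| Either gender, two-sided | 1 - 0.95² | 9.75% |
| Either gender, favouring yoga only | 1 - 0.975² | 4.94% |
| One pooled test, favouring yoga only | 0.05 / 2 | 2.5% |
| Both genders, two-sided | 0.05² | 0.25% |

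**4. Per-gender power at 34 if the pair is controlled at 5%.** Let p be the power at 0.05 and q the power at 0.025. Under Holm, a gender is significant if its p-value is below 0.025, or if it lies between 0.025 and 0.05 while the other gender's is below 0.025. With the same true effect in both genders, this gives q + (p - q) × q. At ρ = 0.5 that is 0.712 + 0.095 × 0.712 = 0.780.

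| ρ | Power at 0.05 | Power at 0.025 | Per-gender power, Holm |
|---|---|---|---|
| 0.3 | 0.666 | 0.550 | 0.614 |
| 0.5 | 0.807 | 0.712 | 0.780 |
| 0.7 | 0.954 | 0.915 | 0.951 |

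Reaching 80% at the 0.025 step alone would need 42 per gender at ρ = 0.5.

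**5. Power on other definitions (ρ = 0.5).** At least one gender significant: 1 - (1 - 0.807)² = 96% uncorrected, and 1 - (1 - 0.712)² = 92% with 0.025 as the first step. One pooled test on 68: 98%.

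**6. Split results.** If the true effect is identical in both genders and each test has the planned 80% power, exactly one is significant with probability 2 × 0.8 × 0.2 = 32%.

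**The case against.** The strongest objection is that 9.75% needs a success rule that the article does not contain. A reader might infer that the trial's error rate simply is 9.75%, or that it is twice a promised 5%. The documents do not support that. They give 5% as the level for each analysis and for each sex-specific sizing, and they promise no trial-wide rate. If both genders had to be significant, the rate would be 0.25%. The hypothesis is also directional, and counting only errors that favour yoga gives 4.94%. These points stand, so the figure must be stated conditionally.

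A reader might also infer that the planned 80% power is lost under correction. That is true only per gender. If either gender counts, power stays above 90% with or without correction, and under Holm the per-gender loss is from about 81% to 78%. The figure of 71% belongs to the 0.025 step alone.

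Three further points have some force. The branch may not be reached, because at 50% attrition the data are pooled. The article plans no claim that the genders differ, so the 32% describes a risk of misreading rather than a planned inference. An analysis plan that is not shown might add a success rule or a correction.

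The last point does not remove the concern. The article itself fixes the level for all analyses and replaces the pooled test with separate ones, and 34 per gender is its stated aim. Any later correction would change the per-sex power that it reports. The genders could be treated as two separate questions, but the article states one hypothesis and none by gender.

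**Conclusion.** The concern holds in conditional form. If at least 34 of each gender complete, one hypothesis is tested twice at 5%, and the plan does not say what confirms it. If either gender suffices, the two-sided chance of at least one false positive is 9.75% (4.94% in favour of yoga, against 2.5% for a single test). If both are required, it is 0.25%.

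These rates assume independent samples and one primary test per gender. The power figures refer to the ANOVA used for sizing and to an assumed correlation of 0.5, the value at which 34 reproduces. Choosing between pooled and separate analysis by numbers recruited, rather than by outcomes, adds no inflation of its own.

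**What to change.** Choose one of two routes and state it in the Data Analysis section.

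- **Preferred:** keep one pooled, gender-adjusted comparison on the BSI as the primary test even when the target is met, and label the gender-specific results secondary or exploratory. Labelling them exploratory without keeping the pooled test would leave no confirmatory analysis, because the present rule pools only when the target is missed.
- **If the gender-specific tests are to carry the primary claim:** control the pair at 5% with Holm (smaller p-value against 0.025, then the other against 0.05). Restate per-gender power at 34 as about 78% with an equal effect in both genders, and 71% at the 0.025 step alone. Give the assumed correlation of 0.5 and the range: 55% to 92% at 0.025 for correlations of 0.3 to 0.7.

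Under either route, allow a statement that the effect differs by gender only from a group-by-gender interaction estimate with its confidence interval.

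The cost is a few sentences and no extra participants. The first route gives up confirmatory status for the gender-specific results. Under Holm, a p-value between 0.025 and 0.05 in one gender alone no longer counts as a positive result, and the stated per-gender power is slightly lower.

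### Reaching 34 of each gender replaces the pooled primary analysis with two separate ones, so meeting the recruitment target removes the better-powered test of the study's own question

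*Protocol article*

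**What the plan says.** The sample-size paragraph (Protocol article, Methods, Participants) is worked out per sex. It begins "Computer required sample size analysis for repeated measures ANOVA within-between interaction, with an effect size of 0.25", uses "a power of 0.80, an alpha error probability at 5"%, is set up "for two groups (yoga and comparison) and two measurements (pre-and post-intervention"), and concludes that this "suggested a sample size of 34 for each sex". The aim follows: "We aim to collect complete data from at least 34 participants of both sexes (34 male and 34 female clients) to perform gender-specific analyses". Then comes the condition: "Gender analyses will only be performed, if this number of participants can be reached".

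Data Analysis turns that condition into a rule with two branches. If the target of 34 or more per sex "is reached, then we will analyze the data separately by gender. Otherwise, the data will be pooled, and no gender-specific results will be presented". The same section applies a 0.05 significance level to every analysis, restricts analysis to complete data, names BSI as the primary outcome without reference to gender, and plans GEE because participants come from three institutions. The hypothesis in the Abstract is about institutionalised adolescents, not about males and females separately.

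**The concern.** Pooling appears only in the branch where the target is missed. Nothing else in the article keeps a pooled test when the target is met, and no group-by-gender term is planned. Followed as written, the rule has two consequences.

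- Which analysis answers the primary question is settled by a count of completers, and the better-recruited study loses the stronger test.
- The single primary question becomes two tests, each at 0.05, and nothing says whether one positive result is enough or both are needed. A study with one significant and one non-significant result would have no planned overall answer.

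**Working it through.** **Inputs.** From Participants: f = 0.25, alpha 0.05, power 0.80, k = 2 groups, m = 2 measurements, 34 per sex, attrition up to 50%, about 120 enrolled. Assumed: pre-post correlation ρ, which is not stated; I use 0.5 and show 0 to 0.7. Equal groups are also assumed. Clustering by institution is ignored, as in the plan's own calculation.

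**Reproducing the plan's figure.** For the within-between interaction, λ = N·m·f²/(1 − ρ), with df₁ = (k − 1)(m − 1) = 1 and df₂ = N − k. At N = 34 and ρ = 0.5, λ = 34 × 2 × 0.0625/0.5 = 8.5 on 1 and 32 df, so power is 0.807. This is the smallest even N that reaches 0.80, so 34 per sex (both groups together) reproduces. With ρ = 0, 0.3 or 0.7 the required N would be 66, 46 or 22.

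**Pooled against separate.** At N = 68, λ = 68 × 2 × 0.0625/0.5 = 17 on 1 and 66 df, so power is 0.982. At N = 67, λ = 16.75 and power is 0.981.

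| ρ | Each sex, N = 34 | Pooled, N = 67 | Pooled, N = 68 |
|---|---|---|---|
| 0 | 0.516 | 0.814 | 0.819 |
| 0.3 | 0.666 | 0.926 | 0.930 |
| 0.5 | 0.807 | 0.981 | 0.982 |
| 0.7 | 0.954 | 0.999 | 0.999 |

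With 34 of one sex and 33 of the other, the rule gives one test at 98% power. One more completer turns this into two tests at 81%.

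**Two tests at 0.05 (ρ = 0.5, same effect in both sexes, independent samples).**

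- At least one false positive when yoga has no effect in either sex: 1 − 0.95² = 0.0975.
- Both significant: 0.807² = 0.651.
- At least one significant: 1 − 0.193² = 0.963.
- Exactly one significant: 2 × 0.807 × 0.193 = 0.31.

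So if success means both, power is 65%. If it means either, power is 96%, but the false-positive rate nearly doubles. In about three studies in ten, an identical effect would look as if it were present in one sex only.

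**Will the split branch occur?** 120 × (1 − 0.50) = 60 completers, fewer than 68. Reaching 68 from 120 needs attrition of at most 1 − 68/120 = 43%, and then only with an even split of the sexes. At 50% attrition, 136 would have to be enrolled.

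**The case against.** The strongest reply is that the sponsor sized the study per sex on purpose. On its own inputs each gender analysis has the planned 80% power, so meeting the target delivers what was designed. That is right: the separate analyses are not underpowered by the plan's calculation. It does not explain why the pooled test of the stated hypothesis should disappear.

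Second, the sentence in Participants could be read as adding gender analyses to a pooled one, and the article condenses a fuller plan. Taken alone, that sentence allows this. The word that opens the second branch in Data Analysis does not, so the text needs correcting even if the intention was sound.

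Third, the split may never be triggered. At the attrition limit the pooled branch applies. But 34 + 34 is the declared aim, so the rule must work when the aim is met.

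Several stronger readings are tempting and are not supported:

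- **Severe loss of power.** A reader might take a between-group difference in change of d = 0.5, which Data Analysis labels medium, and find 53% power pooled against 29% per sex. That changes the effect size: f = 0.25 at ρ = 0.5 corresponds to a difference of 1.0 SD. At d = 0.5 the pooled analysis is underpowered too, so the figures mainly show a dispute over effect size.
- **The sample is always halved.** This is exact only when the sexes complete in equal numbers.
- **The error rate is 9.75%.** This requires no effect in either sex, independent tests, and either result counting as success. The article states no such success rule.
- **The plan fails to answer a question about gender differences.** It does not claim to ask one. The 31% figure is a caution about interpretation, not a defect in a stated aim.
- **The threshold lets through badly unbalanced groups.** It does count each sex in total, and participants choose their group, but the article gives no expected imbalance. A moderate one costs little: 20/14 within a sex has 79% power at a 1.0 SD difference, against 81% for 17/17.

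**Conclusion.** The point holds as a fault in the decision rule. As written, meeting the target of 34 of each gender removes the only planned pooled test of a hypothesis that concerns adolescents as a whole. On the plan's inputs with ρ = 0.5 assumed, the primary question goes from one test at 98% power to two at 81%; over ρ from 0 to 0.7, pooled power is 82% to 99.9% and per-sex power 52% to 95%. The larger gap is in interpretation, because no rule combines the two primary results. The conclusion rests on reading the Data Analysis rule literally, and it matters only if attrition from about 120 enrolled stays at or below roughly 43% with the sexes evenly represented.

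**What to change.** In both Participants and Data Analysis, state that the primary analysis of BSI pools all completers and adjusts for sex, whatever numbers are reached. The GEE already planned can carry the sex term. If 34 of each gender is reached, add as secondary analyses the sex-specific estimates with confidence intervals and a group-by-sex interaction from the same model, and say that no conclusion about a gender difference will be drawn from comparing separate p-values. The 34-per-gender condition then decides only whether these secondary results are presented.

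The cost is a change of wording, with no new data, participants or procedures. The one real concession is that the gender-specific analyses become secondary.
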